## 4.4 Inclusion Criteria Social Network Member

1. Male or Female 18 years of age or older
2. Access to the internet or a smartphone

## 4.5 Exclusion Criteria Social Network Member

1. Speaks a language other than English or Spanish

## 4.6 Lifestyle Considerations

**Not applicable**

## 4.7 Screen Failures

Screen failures are defined as participants who consent to participate in the clinical trial but are not subsequently randomly assigned to the study intervention or entered in the study. A minimal set of screen failure information is required to ensure transparent reporting of screen failure participants, to meet the Consolidated Standards of Reporting Trials (CONSORT) publishing requirements and to respond to queries from regulatory authorities. Minimal information includes demography, screen failure details, eligibility criteria, and any serious adverse event (SAE). Individuals who do not meet the criteria for participation in this trial (screen failure) because of an active enrollment in a weight loss program, food insecurity, or lack of clearance from a medical provider may be rescreened. Rescreened participants should be assigned the same participant number as for the initial screening.

## 4.6 Strategies for Recruitment and Retention

Recruitment Strategies:

- An estimated 800 Black or Hispanic individuals 18 years of age or older will need to be screened in order to reach the target enrollment of 132 participants.
- The anticipated accrual rate is 8 participants per month (6% of target enrollment)
- Recruitment will take place at four outpatient clinic sites Weill Cornell Internal Medicine Associates, Weill Cornell Urology @ Brooklyn, Weill Cornell Urology @ Upper East Side, and Weill Cornell Primary Care at Lower Manhattan.
- Potential participants will be identified through a TRAC request in EPIC specific to those clinical sites. Study staff will contact the medical provider to verify that the participant is fit to potentially participate in the study and ask their permission to contact the potential participant. Participants will be contacted via phone call, email or regular mail based on their indicated preferences for communication in the electronic health record.
- Recruitment strategies will include mailing potential participants flyers describing the study with the study team contact information.

Retention Strategies:

- - Collection of monthly screening, enrollment, and retention logs
  - Index participants will be compensated $25 for each in person visit
  - Social network participants will be compensated $25 for each completed survey
  - Participants will receive text and call reminders for each scheduled visit

# 5. Registration Procedures

## 5.1 Subject Registration (WCM only)

Subjects will be registered within the WRG-CT as per the standard operating procedure for Subject Registration.

## 5.2 Subject Registration (Sub-sites)

**Not applicable**

# 6. Study Procedures

## 6.1 Schedule of Assessments

Table 1. Schedule of trial events

| **Study Measures and Assessment Schedule Week #** | | | |
| --- | --- | --- | --- |
| **Construct** | **Measure** | **Index** | **SN** |
| **Personal** | - Socio-demographic and biology: age, sex, race/ethnicity, marital status, education, employment, occupation, medical conditions, medications, food security  - Objective anthropometrics: height, weight, BMI, waist to hip ratio, waist circumference  - Self-reported height and weight *(participating social network only)*  - Self-efficacy: 9 item self-efficacy scale  - Perceived Stress: Cohen's perceived stress scale 3-item  - Positive Affect: The Positive and Negative Affect Schedule (PANAS) | 0  0, 8, 16, 24  0, 24  0, 24  0, 24 | 0  0, 24  0, 24  0, 24  0, 24 |
| **Environmental** | - Support and Undermining: Sallis Social Support and Eating Habits/ Exercise  - Health norms: Weight Related Social Norms Scale  - Social network interview: structure, composition, and functions (interpersonal conflict, undermining, communication, support, obesity-related norms)  - Communal Coping: verbal encouragement and collaborative problem solving | 0, 24  0, 24  0, 24  0,8,16,24 | 0, 24 |
| **Behavioral** | - Self-reported physical activity: Paffenbarger Physical Activity Questionnaire  - Objectively measured physical activity: Fitbit fitness tracker  - Dietary intake: three-day food record | 0, 8, 16, 24  0, 8, 16, 24  0, 8, 16, 24 | 0, 24  0, 24 |

### **6.1.1 Screening Visit (*14 days before start of treatment*)**

- Informed consent

### **6.1.2 Treatment Phase**

Eligible participants will be randomly assigned to the social network intervention or control groups in a 1:1 ratio using a numerical randomization scheme developed by the statistical team. Following randomization, participants that are randomized to the social network intervention group will complete 3 in person communication skills sessions with their social network members during weeks 3, 5, and 15. Instead of completing communication skills sessions, participants randomized to the control group will complete regular virtual lifestyle coaching sessions with the study team that consists of the following topics: Keep your health healthy (week 3), Eat well away from home (week 5), and Social Cues (Week 15). All other sessions will focus on the topics below and will be the same across both treatment groups.

Note: The weeks that are not listed in the treatment phase below are weeks that will be treatment breaks.

### **Visit 1 (Intake; Week 0)**

### Review accuracy of completed baseline survey (10 minutes)

### Conduct anthropometrics (15 minutes)

### Conduct Social Network Survey (15 minutes)

### Set up Program Equipment & set coaching schedule (45 minutes)

### **Visit 2 (Track your food and physical activity; Week 1)**

- - - - 1. Check in (5 minutes)
        2. Review self-regulations skills (10 minutes)
        3. Review workbook lesson (30 minutes)
        4. Homework & set new/or revise SMART Goal (5 minutes)

### **Visit 3 (Dietary Counseling, Week 2)**

- - - - 1. Review of 3 day food record (10 minutes) Activities (40 minutes)
        2. Review workbook lesson (30 minutes)
        3. Homework & set new/or revise dietary SMART Goal (5 minutes)

### **Visit 4 (Communication Skills or Keep Your Heart Healthy, Week 3)**

### Check in (5 minutes)

### Review self-regulations skills (10 minutes)

### Review workbook lesson (30 minutes)

### Homework & set new/or revise SMART Goal (5 minutes)

### **Visit 5 (Find Time for Fitness and Get Active, Week 4)**

### Check in (5 minutes)

### Review self-regulations skills (10 minutes)

### Review workbook lesson (30 minutes)

### Homework & set new/or revise SMART Goal (5 minutes)

### **Visit 6 (Communication Skills or Eat Well Away from Home, Week 5)**

- - - - 1. Check in (5 minutes)
        2. Review self-regulations skills (10 minutes)
        3. Review workbook lesson (30 minutes)
        4. Homework & set new/or revise SMART Goal (5 minutes)

### **Visit 7 (Burn more calories that you can take it, Week 7)**

### Check in (5 minutes)

### Review self-regulations skills (10 minutes)

### Review workbook lesson (30 minutes)

### Homework & set new/or revise SMART Goal (5 minutes)

### **Visit 8 (Dietary Counseling, Week 8)**

### Review of 3 day food record (10 minutes)

### Review workbook lesson (30 minutes)

### Homework & set new/or revise dietary SMART Goal (5 minutes)

### **Visit 9 (Manage Stress, Week 9)**

- - - - 1. Check in (5 minutes)
        2. Review self-regulations skills (10 minutes)
        3. Review workbook lesson (30 minutes)
        4. Homework & set new/or revise SMART Goal (5 minutes)

### **Visit 10 (Get more active, Week 11)**

- - - - 1. Check in (5 minutes)
        2. Review self-regulations skills (10 minutes)
        3. Review workbook lesson (30 minutes)
        4. Homework & set new/or revise SMART Goal (5 minutes)

### **Visit 11 (Take charge of your thoughts, Week 13)**

- - - - 1. Check in (5 minutes)
        2. Review self-regulations skills (10 minutes)
        3. Review workbook lesson (30 minutes)
        4. Homework & set new/or revise SMART Goal (5 minutes)

### **Visit 12 (Communication Skills or Social Cues, Week 15)**

- - - - 1. Check in (5 minutes)
        2. Review self-regulations skills (10 minutes)
        3. Review workbook lesson (30 minutes)
        4. Homework & set new/or revise SMART Goal (5 minutes)

### **Visit 13 (Dietary Counseling, Week 16)**

- - - - 1. Review of 3 day food record (10 minutes)
        2. Review workbook lesson (30 minutes)
        3. Homework & set new/or revise dietary SMART Goal (5 minutes)

### **Visit 14 (Staying Motivated, Week 20)**

- - - - 1. Check in (5 minutes)
        2. Review self-regulations skills (10 minutes)
        3. Review workbook lesson (30 minutes)
        4. Homework & set new/or revise SMART Goal (5 minutes)

### **Follow-up Phase**

### **Visit 15 (Close out; Week 24)**

### Close out survey for control group, and social network intervention group and their social network members

### Preventing relapse nutrition session for the social network intervention group and the control group

# 7. Study Intervention

##

## 7.1 Study Intervention Description

The study intervention is a social network intervention which consists of the involvement of participants social network members. Study participants will complete 3 communication skills sessions with their social network members which will involve the creation and utilization of positive affirmations and strategies that social network members will use to reduce undermining participants during their weight loss journey.

- Communication Skills session outline: See Appendix

## 7.2 Availability

The intervention is an investigational agent that uses scripts and worksheets that are created by the study team. The intervention does not require any supplies from Pharmaceutical or Device Companies.

## 7.3 Acquisition and Accountability

Retention log – The study staff will maintain a record of participants who complete the social network intervention.

## 7.4 Formulation, Appearance, Packaging, and Labeling

Please see appendix for worksheets.

## 7.5 Product Storage and Stability

**Not Applicable**

## 7.6 Preparation

**Not applicable**

## 7.7 Dosing and Administration

Participants receiving the social network intervention will complete communication skills sessions during weeks 3, 5, and 15 of the study. Participants in the control group will complete regular discussion sessions during week 3,5, and 15 of the study which will consist of the following topics: Move those muscles, Keys to health eating out, and social cues, respectively. Those who continue in the study will only receive each session one time.

### **7.7.1 Dosing Delays/Dose Modifications**

**Not applicable**

## 7.8 General Concomitant Medication and Supportive Care Guidelines

**Not applicable**

## 7.9 Duration of Therapy and Criteria for Removal from Study

All control and treatment group participants will receive the study intervention for 24 weeks. A subject’s follow-up in the study will end after one of the following applies:

- Subject’s voluntary withdrawal
- Subject lost to follow-up
- Adverse medical event in which the participant has been advised to halt all physical activity or needs to initiate a new medically prescribed diet
- Subject death
- Completion of all scheduled study follow-up appointments

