## 7.10 Duration of Follow Up

Subjects will be followed for 6 month after removal from study or until death, whichever occurs first. Subjects removed from study for unacceptable adverse events will be followed until resolution or stabilization of the adverse event.

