# 8. Study Intervention Discontinuation and Participant Discontinuation/Withdrawal

## 8.1 Discontinuation of Study Intervention

Criteria for discontinuing the study intervention is as follows:

- Cardiovascular, pulmonary, hypoglycemia: Adverse events will be defined as cardiovascular (MI, CVA, death), acute shortness of breath, or hypoglycemia precipitated by changes in dietary intake or the physical activity chosen for the study requiring hospitalization/emergency room visit or a physician office visit. Non-routine office visits for cardiac or pulmonary disease or diabetes are expected and not serious unless they lead to the above events.
- Major depressive episode or anxiety attack: Infrequent likelihood. A participant may become depressed, anxious or severely embarrassed if friends/family/acquaintances find out that the person is participating in and/or not losing weight in the program. Patients have the option of not answering any questions they do not want to. As this is a voluntary study, a participant is free to withdraw from the study at any point if they feel uncomfortable or do not want to continue.
- Medication Side Effects: Infrequent risks. The study does not prescribe medication. Weight loss can cause a change in the dose of medication needed to treat common health conditions such as hypertension, diabetes and thyroid dysfunction. Participants will be required to communicate their participation in the study along with their weight loss to a primary care physician.
- Musculoskeletal: Musculoskeletal injury due to the physical activity chosen for this study resulting in hospitalizations, emergency department visits, or treatment for fracture in any setting will be considered expected serious adverse events. Non-routine office visits for musculoskeletal injury are expected and not serious unless lead to the above events. Temporary minor incapacitation due to muscle soreness is also expected and not serious.

Discontinuation from the social network intervention does not mean discontinuation from the study, and remaining study procedures should be completed as indicated by the study protocol. If a clinically significant finding is identified (including, but not limited to changes from baseline) after enrollment, the investigator or qualified designee will determine if any change in participant management is needed. Any new clinically relevant finding will be reported as an adverse event (AE).

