## 12.1 Study Design/Endpoints

This randomized controlled trial will use the following primary endpoints as the promising range to justify further testing of this agent:

- At least 75% attendance rate for the participant and their network members in their respective behavioral coaching sessions.
- 80% of participants or more to have at least one network member engage in the study.
- 85% of participants and their network members or more to complete the final study assessment.

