### **12.4.2 Analysis of Secondary Endpoints**

We will examine summary statistics, histograms, and scatter plots of the measured covariates and outcomes for outliers and data trends. Analyses of differences between those completing and not completing the study and the within-group changes during the intervention will be performed according to modified intention-to-treat principles. Multivariate linear regression (MLR) models will be used to examine the relationship between changes in the social network processes and exposure (the social network lifestyle intervention vs the lifestyle intervention), adjusted for covariates selected from univariate analyses; potential covariates for MLR are categorized by theoretical construct. We will also explore the effect of gender by including a three-way interaction (gender*social support*weight loss), although we recognize that we might not have enough power to detect such interactions.

To further explore the effect of the intervention, we will do sensitivity analysis: (1) Multivariable linear regression using weight loss as continuous outcome variables (a change in weight and percent weight change), adjusting for baseline covariates distributed differently between intervention groups; (3) test interaction terms between treatment group and other covariates; and (4) examine completers only.

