### **12.6.2 Evaluation of Response**

All subjects included in the study will be assessed for response to treatment if they have received at least once coaching session after randomization given the intent-to-treat analysis that will be applied.

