## Measurement and reporting of adverse events

We plan to collect symptom data related to increased physical activity and adverse events as part of the routine coaching sessions at week 3, 4, 5, 7, 9, 11, 13, 15, and 20. We plan to present unblinded adverse events data to the study statistician, the PI, and the safety officer throughout this trial. There is some level of injury expected from individuals potentially increasing their physical activity although the recommended mode of physical activity will be walking and reducing sedentary time. In our previous RCT study of 405 adults enrolled in a lifestyle intervention study and followed over 12 months, 13 (16%) expected adverse events (were likely related to the study protocol. Among all AE's, 17 (21%) were related to musculoskeletal complaints. There were 7 (9%) cardiovascular events and 17 (21%) pulmonary events. 73% of the total adverse events (81) were rated as unlikely or unrelated to the intervention. ^28^

Definitions of expected adverse events for this study:

*Cardiovascular, pulmonary, hypoglycemia:* Adverse events will be defined as cardiovascular (MI, CVA, death), acute shortness of breath, or hypoglycemia precipitated by changes in dietary intake or the physical activity chosen for the study requiring hospitalization/emergency room visit or a physician office visit. Non-routine office visits for cardiac or pulmonary disease or diabetes are expected and not serious unless they lead to the above events.

*Major depressive episode or anxiety attack:* Infrequent likelihood. A participant may become depressed, anxious or severely embarrassed if friends/family/acquaintances find out that the person is participating in and/or not losing weight in the program. Patients have the option of not answering any questions they do not want to. As this is a voluntary study, a participant is free to withdraw from the study at any point if they feel uncomfortable or do not want to continue.

*Medication Side Effects* Infrequent risks. The study does not prescribe medication. Weight loss can cause a change in the dose of medication needed to treat common health conditions such as hypertension, diabetes and hypothyroidism. Participants will be required to communicate their participation in the study along with their weight loss to a primary care physician.

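### Section 7.9 ends follow-up after certain adverse events, against 7.10 and in part against 8.1, so week-24 data can be lost for health reasons

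*Protocol*

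**What the plan says.** Four sections of the Protocol bear on what happens after a health event.

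- **7.9** gives a list of conditions, any one of which closes a subject's follow-up. One is "Adverse medical event in which the participant has been advised to halt all physical activity or needs to initiate a new medically prescribed diet". The wording leaves no discretion and makes no exception for week 24.
- **7.10** says "Subjects will be followed for 6 month after removal from study or until death, whichever occurs first", and then "Subjects removed from study for unacceptable adverse events will be followed until resolution or stabilization of the adverse event". The first sentence does not say what is to be collected.
- **8.1** lists health events that stop the intervention: cardiovascular, pulmonary, hypoglycemic, psychiatric, medication-related and musculoskeletal. It then says "Discontinuation from the social network intervention does not mean discontinuation from the study, and remaining study procedures should be completed".
- **8.2** allows, but does not require, an investigator to withdraw a participant because of an adverse event.

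Week 24 matters for several outcomes. Section 12.1 has as a primary endpoint "85% of participants and their network members or more to complete the final study assessment". Section 12.4.1 defines retention as 24-week completers among those who completed baseline. Weight, diet and activity are measured at the same time point (Table 1 in 6.1). Section 12.4.2 says the analyses of within-group change, and of completers against non-completers, "will be performed according to modified intention-to-treat principles". Section 12.6.2 says anyone with at least one coaching session after randomization is assessed for response, "given the intent-to-treat analysis that will be applied".

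**The concern.** Advice to stop exercising, or a new diet ordered by a clinician, is a reason to stop the activity or diet coaching. It is not in itself a reason to forgo a survey and a weigh-in. If staff follow 7.9, they stop collecting data on a participant who is alive and still consenting, and the reason is that participant's health. Health is plausibly related to weight, diet and activity, so the missing values would not be a random subset. An analysis plan can model such missing values, but it cannot recover data that the protocol told staff not to collect.

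The protocol also gives different instructions for the same person. Staff at four recruiting sites could resolve this differently. Because the sentence in 8.1 names only the social network intervention, they could also resolve it differently by arm.

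**Working it through.** **1. The rules side by side**

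| Section | Trigger | Consequence | Arm |
|---|---|---|---|
| 7.9 | Advice to stop all activity, or new prescribed diet | Follow-up ends | Both |
| 7.10, first sentence | Any removal from study | Six months of follow-up, content unspecified | Both |
| 8.1 | Listed health events | Intervention stops, remaining procedures completed | Social network arm named |
| 8.2 | Adverse event, participant's interest | Withdrawal possible | Both |

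7.9 and 7.10 conflict for every removal under 7.9. 7.9 and 8.1 conflict only where the triggers overlap, because 8.1 mentions neither advice to stop all activity nor a new diet. An MI or an exercise-related fracture with such advice meets both. No text sets an order of precedence.

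**2. Does the 7.10 window reach week 24?** Take removal at week t, with t at or after 0 because randomization follows the baseline network interview. Six months is about 26 weeks, so the window closes at about t + 26, which is always later than week 24. The window is long enough. What is missing is any statement that the week-24 assessment takes place within it.

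**3. The plan's power figures.** Inputs (section 15, Stopping rules): 132 index participants, 1:1 allocation, difference 8 lb, SD 10.4. Alpha is not stated there; 0.05 two-sided is assumed. With n = 66 × (1 − d) per arm, power = Φ(8 / (10.4 × √(2/n)) − 1.96).

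| Dropout d | n per arm | Normal approximation | t-test | Stated |
|---|---|---|---|---|
| 15% | 56.1 | 0.983 | 0.981 | 98% |
| 30% | 46.2 | 0.959 | 0.954 | 96% |
| 40% | 39.6 | 0.928 | 0.918 | 92% |
| 50% | 33.0 | 0.878 | 0.868 | 88% |

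The stated figures reproduce. A further 5% lost on top of 15% gives n = 66 × 0.80 = 52.8 and power 0.977.

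**4. How many people?** No rate for the 7.9 triggers is given. The nearest source is section 15, Measurement and reporting of adverse events: "In our previous RCT study of 405 adults enrolled in a lifestyle intervention study and followed over 12 months", with 7 cardiovascular, 17 musculoskeletal and 17 pulmonary events. Assume a constant rate and the same rate in this population. Expected events are then k/405 × 132 × 24/52.

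- Cardiovascular, k = 7: 1.05
- Musculoskeletal, k = 17: 2.56
- Both, k = 24: 3.61 (3.61/132 = 2.7%)
- Adding pulmonary, k = 41: 6.17 (6.17/132 = 4.7%)

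These are events, not persons, and only some would carry advice to stop all activity. New prescribed diets are not counted at all. The figures are a rough guide and not a bound in either direction.

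**5. Room on the completion endpoint (index participants only).** 0.85 × 132 = 112.2, so 113 completers are needed and 19 non-completers can be absorbed. The planned 15% attrition is 0.15 × 132 = 19.8, which already uses that room. As an illustration, assume 10% attrition from other causes, add an assumed share removed under 7.9, and treat completion as binomial:

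| Removed under 7.9 | Completion probability | Chance of at least 113 of 132 |
|---|---|---|
| 0% | 0.90 | 0.96 |
| 1% | 0.89 | 0.91 |
| 3% | 0.87 | 0.73 |
| 5% | 0.85 | 0.48 |

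Both the 10% and the removal shares are assumptions. The table shows sensitivity and is not a forecast.

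**The case against.** The strongest reply is that the protocol has two deliberate tiers: 7.9 removes people from the study, and 8.1 stops only the intervention. Section 4.3 supports this, since it excludes illness or injury that prevents regular activity and lack of medical clearance, and 8.2 permits withdrawal of someone who newly meets an exclusion. This stands to the extent that a reader should not infer that 8.1 contradicts 7.9 for every triggering event. It does not settle events that meet both lists. Nor does it explain why removal must cost the week-24 visit.

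A second reply is that 7.10 already provides follow-up after removal, so the loss of week 24 is not certain. This also stands. 7.10 softens the problem and its window is long enough, so its first sentence should be completed and not deleted. As written, however, it names no assessment and contradicts 7.9.

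Third, completion is not made missing. Under 12.4.1 a removed participant who completed baseline is an observed non-completer in the denominator, which is a legitimate way to count in a feasibility trial. This is right. The harm on that endpoint is that the protocol itself creates some of the non-completion. Missing data in the strict sense arise only for weight and the other secondary measures.

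Fourth, 12.6.2 says who is assessed and does not promise complete data, and 12.4 already plans comparisons of completers with non-completers. That is fair, so the intention-to-treat wording is supporting context here and not a separate breach.

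**Conclusion.** The point holds as a conflict between 7.9 and 7.10 for all removals, and between 7.9 and 8.1 for events that meet both lists, with the control arm unclear in 8.1. Followed literally, 7.9 loses week-24 weight and other secondary outcomes for health reasons and lowers the completion rate.

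The effect is probably a few index participants. That judgement rests on the constant-rate scaling from the earlier trial and on the view that only some of those events would bring advice to stop all activity. The true number cannot be derived from the document.

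Two stronger readings are tempting and unsupported. One is that about six participants is a ceiling; it is not, because diet triggers are uncounted and events are not persons. The other is that the trial loses power; it does not to any material degree, since even a further 5% lost moves power only from 0.983 to 0.977. What is at stake is bias in the week-24 comparison and a completion benchmark with little room. The correction should be made because it is cheap and removes an avoidable source of health-related missing data.

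**What to change.** - **7.9:** state that an adverse event of this kind stops only the coaching sessions or the activity and diet components, not study follow-up.
- **8.1:** reword the retention sentence so that it refers to the study intervention in either arm.
- **7.10:** add that follow-up after removal includes the scheduled week-24 assessment for every randomized participant who is alive and has not withdrawn consent. Keep the second sentence, on following the adverse event, as it is; it is sound safety follow-up.

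The cost is a wording amendment and a few extra week-24 contacts. Sample size and stated power do not change.
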